## Analysis Summary

**Study Title:** Prospective, Single-Arm, Open-Label, Multicenter Study of Hypotension Prevention and Treatment in Patients Receiving Arterial Pressure Monitoring With Acumen™ Hypotension Prediction Index Feature Software (Clinical Protocol 2018-15)

**Primary Objective:** To determine whether the use of the Acumen™ HPI Feature Software to guide intraoperative hemodynamic management in non-cardiac surgery reduces the duration of intraoperative hypotension (defined as MAP < 65 mmHg for at least 1 minute) as compared with a historic retrospective control group.

**Primary Effectiveness Endpoint:** Duration (t [min]) reduction of intraoperative hypotension (defined as MAP < 65 mmHg for at least 1 minute) as compared with a historic retrospective control group.

**Primary Safety Endpoints:** Serious adverse events through 30 days as indicated below:

1. Serious Intraoperative and postoperative complications between each cohort;
2. Device-related serious adverse events.

**Secondary Effectiveness Endpoint:** The determination of total area under the curve (time and MAP) for IOH in each subject. This endpoint is correlated with the duration and a descriptive analysis of this endpoint will be presented with the mean, standard deviation, median, minimum and maximum.

**Secondary Safety Endpoint:** Percentages of subjects experiencing at least one of the following: postoperative episodes of non-fatal cardiac arrest, in-hospital death, stroke, AKI and MINS within 30 days of the procedure in the control and treated arms, respectively.

### Additional Endpoints:

1. Reduction of IOH duration at MAP  $\leq$  60 mmHg;
2. Area under threshold MAP < 65 mmHg
3. Acute kidney injury (AKIN criteria);
4. Quality of recovery (QoR-15) on postoperative day 3;
5. Postoperative morbidity survey (POMS) on postoperative day 3;
6. Amount of red blood cells infused (ml packed red blood cells);
7. Amount of intraoperative fluid (crystalloid and colloid);
8. Amount of vasoactive medications (i.e. phenylephrine, ephedrine, nor-epinephrine, (1)epinephrine, dobutamine);
9. Advanced hemodynamic variables at 20-sec intervals:
  - a. Hypotension prediction index (HPI)
  - b. Cardiac output (CO);
  - c. Cardiac Index (CI);
  - d. Stroke Volume (SV)
  - e. Stroke Volume Index (SVI);
  - f. Stroke Volume Variation (SVV);
  - g. Dynamic arterial elastance (Edyn);
  - h. Maximal slope of the arterial pressure upstroke (dP/dt);
  - i. MAP & PR
10. Hospital length of stay;
11. ICU Hospital length of stay
12. Hospital readmission within 30 days;
13. Cardiovascular mortality at 30 days;

14. Composite of systemic inflammatory response syndrome (SIRS) and at least one major organ dysfunction for renal, cardiovascular, respiratory, neurologic and coagulation systems by day 7 after surgery (2);
15. Acute respiratory distress syndrome (3);
16. Acute pulmonary edema (3);
17. Superficial or deep surgical site infection (3);
18. Hospital acquired infection (4);
19. Ventilator time.

**Patient Population:** Subjects recruited and enrolled should be classified as American Society of Anesthesiologist (ASA) physical status 3-4 who are scheduled for moderate-to-high-risk non-cardiac surgery and will be receiving pressure monitoring with an arterial line. Potentially qualifying patients will be evaluated during their preoperative anesthesia clinic visits. ...

**Study Design:** A prospective, single-arm, open-label, multicenter post-approval study to determine whether the use of the Acumen™ HPI Feature Software to guide intraoperative hemodynamic management in non-cardiac surgery reduces the duration of intraoperative hypotension below a threshold of Mean Arterial Pressure (MAP).

**Number of Patients:** Up to 485 eligible subjects at up to 20 US study sites. The control group is comprised of 19446 patients. This number of controls is fixed and will not be altered.

## Statistical Procedures

---

### I. Introduction

Hemodynamic parameters that until recently were considered clinically acceptable, for instance, a MAP of 65 mmHg, are associated with both myocardial and renal injuries. At lower pressures, the association was stronger and only brief exposures were required. Associations based on relative thresholds were no stronger than those based on absolute thresholds. A strategy aimed at maintaining MAP above 65 mmHg appears to be as good as one based on the percentage reduction from baseline. (See figure 1) Absolute thresholds are easier to use in that they do not require a reliable baseline pressure and can thus more easily be incorporated into decision support systems (Salmasi et al. (2017)).

Multiple studies have also demonstrated that hypotensive duration is an important determinant of the likelihood, and possibly even the severity, of unfavorable outcomes (Meng et al. (2018)). Precise treatment of perioperative hypotension should be based on a reference to the patient's baseline measurements of BP, cardiac output, stroke volume, heart rate, and systemic vascular resistance. The execution of this proposal demands advanced hemodynamic monitoring that assesses volume and flow (Meng et al. (2018)).

The effects of intra-operative hypotension (IOH) on postoperative safety is a topic of great clinical concern. The association of IOH with postoperative death or substantial morbidity within 30 days has prompted clinicians to attempt to control IOH. The impact of this clinical concern is to question the ethics of having a concurrent untreated control group for any therapeutic agent to reduce the duration of IOH in non-cardiac surgical procedures. As a result of this concern, Edwards Life Sciences has devised a method to use a control population taken from a managed registry with patient-level data on non-cardiac surgical procedures. The registry described below provides the IOH duration of at least one minute duration for a recent time period expected to be unaffected by implementation of therapeutic methods to reduce the impact of IOH.

### II. Study Design

This study is a prospective single-arm open-label multi-center post-approval study to determine whether the use of the Acumen™ HPI Feature Software to guide intraoperative hemodynamic management in non-cardiac surgery reduces the duration of intraoperative hypotension below a threshold of Mean Arterial Pressure (MAP). The comparison group for this study is a retrospective historical control group with patient-level data from the Multicenter Perioperative Outcomes Group (MPOG). The intention is to conduct the active therapeutic study at clinical centers enrolled in MPOG with HPI study patients being selected from the same centers. The methods described below are intended to provide a comprehensive analysis of the safety and effectiveness of the study data.

### III. Analysis Objectives

The Primary Objective is to determine whether the use of the Acumen™ HPI Feature Software to guide intraoperative hemodynamic management in non-cardiac surgery reduces the duration of intraoperative hypotension (defined as MAP < 65 mmHg for at least 1 minute) as compared with a historic retrospective control group.

### IV. Analysis Populations

#### A. Intent-to-Treat (ITT) Population

All subjects enrolled in the study comprises the intention-to-treat population. A subject will be considered enrolled in the study once the subject has signed the informed consent, has been assigned a Study Identification Number (SID), an arterial line has been placed and FloTrac IQ has been connected.

## **B. Full Analysis Set (FAS) Population**

All enrolled subjects who undergo surgery of at least 3 hours duration and have one postoperative assessment comprises the full analysis set.

## **C. Completed (Evaluable) Cases (CC) Population**

All patients who have had at least a 3-hour surgery and complete the 30-day follow-up comprises the completed cases population.

## **D. Per Protocol (PP) Population**

All completed case subjects who do not have a protocol violation that could affect the primary endpoints of the study comprise the completed cases population.

### **1. Sample Size Computation**

Recent analysis from the Multicenter Perioperative Outcome Group (MPOG) evaluated the mean duration of IOH in a subset of participating sites, during calendar year 2017, who met the eligibility criteria of this HPI Study. The analysis resulted in a total of 19446 patients with at least one minute of IOH and demonstrated a mean duration of IOH of 28.2 minutes with standard deviation 42.5.

It is anticipated that the HPI system will reduce that number of minutes by about 25%. Because the size of the standard deviation (SD) of the minutes in IOH decreases with decreasing mean. Estimates from other literature suggest that the SD is a similar fraction of the mean within the range. For this computation we assume that the ratio of the standard deviation to the mean remains constant. The ratio of the standard deviation of the mean from these data is  $42.5/28.2 = 1.50$ . To protect against the uncertainty of the ratio under powering the study, additional computations were done to make the estimate more conservative with a SD to mean ratio of 1.65. The minimum recommended required sample size, using Pass 14, of 389 completed subjects for 90% power for a one-sided  $\alpha = 0.025$  test which were derived from the additional computations of standard deviation ratios. Assuming an attrition for a less than 3-hour surgery of 10% and a small loss to follow-up of 4%, the recruited sample size should be  $389/0.86 \approx 452$  for 90% power in the Pivotal cohort. Therefore, the sample size for this study will be capped at 485, including up to 33 roll-in subjects and up to 452 Pivotal subjects, for a minimum of 90% power. Roll-in subjects will be analyzed separately from Pivotal subjects.

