## **VI. Multiplicity**

The testing for the primary effectiveness analysis will be a one-sided 0.025 test. The primary effectiveness analysis must meet its objective of statistical significance. After analysis of the primary effectiveness endpoint, if the primary analysis results in statistical significance, the descriptive secondary effectiveness endpoints will be presented with nominal two-sided 95% confidence intervals. Thus, the study will be protected from alpha inflation by the closed form hierarchical method. Multivariate analyses are considered supportive without control of alpha and the additional endpoint analyses are likewise supportive without control of alpha.

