## D. Primary Effectiveness

Recall that the study subjects were drawn from the same study sites that were used for the MPOG estimates from the control population. Because the sites may represent different patient populations, it is likely that the estimates from the site may be heterogeneous as were the estimates for the control MPOG sample. In an ideal world the proportion of subjects in the study will be similar to that from the MPOG controls, but the dynamics of study conduct usually result in a different subject distribution depending on which study sites were entered into the study earlier rather than later. In order to provide an estimate from the study sample that is most comparable to the controls adjusting for site the primary effectiveness endpoint will be done with a weighted average of site means and standard deviations as described below.

The study subjects will have the mean and standard deviation of the durations of IOH during the study computed by study site. To generate an estimate across the range of estimates for comparison to the MPOG controls, the estimates from each study site will be weighted and combined in the same proportion of subjects that were included in the control sample from MPOG. This method is analogous to direct standardization used in epidemiology (Fleiss et al (2003)). This weighted average and its properly computed standard deviation will be compared to the estimates obtained from MPOG by a one-sided unequal variance two-sample t-test. If this test is statistically significant with  $P<0.025$ , the primary effectiveness endpoint will be a success. If the proportion of subjects in the

control sample is  $p_k$  for study site  $k$  and the estimate of the mean from study site  $k$  is  $\bar{x}_k$ , then the study estimate from the interim sample for the overall mean is given below.

$$\bar{x} = \sum_k p_k \bar{x}_k.$$

If the standard deviation for study site  $k$  is  $s_k$ , then the estimate of the interim standard deviation is given below.

$$s = \sqrt{\sum_k (p_k s_k)^2}.$$

The test statistic for the interim is taken from the formula below.

$$t = \frac{\bar{x} - \bar{x}_{MPOG}}{\sqrt{\frac{s^2}{n} + \frac{s_{MPOG}^2}{n_{MPOG}}}}.$$

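### The 389 completed subjects do not follow from the stated 25% reduction and SD/mean ratio of 1.65, and the 90% power minimum makes no allowance for the site-weighted primary test

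*SAP*

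**What the plan says.** SAP section V.A.1 (Sample Size Computation) takes its control figures from MPOG, which "demonstrated a mean duration of IOH of 28.2 minutes with standard deviation 42.5". The Analysis Summary fixes the size of that group: "The control group is comprised of 19446 patients". On the effect, section V.A.1 states: "It is anticipated that the HPI system will reduce that number of minutes by about 25" percent. It then assumes that the treated SD shrinks in proportion to the mean, observes a ratio of 42.5/28.2 = 1.50, and reports that "additional computations were done to make the estimate more conservative with a SD to mean ratio of 1.65". From these computations it gives a minimum requirement "of 389 completed subjects for 90% power for a one-sided" test at 0.025. Section VI (Multiplicity) confirms the level: "The testing for the primary effectiveness analysis will be a one-sided 0.025 test".

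Allowing 14% attrition, section V.A.1 recruits 452 Pivotal subjects and caps the study at 485, "including up to 33 roll-in subjects and up to 452 Pivotal subjects, for a minimum of 90% power".

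Section IX.D (Primary Effectiveness) defines the test. The site estimates "will be weighted and combined in the same proportion of subjects that were included in the control sample from MPOG", and the weighted mean is compared with MPOG by an unequal-variance t-test. The same section expects the study's site mix to differ from the control mix.

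**The concern.** Section V.A.1 states every input needed to recompute 389, and the recomputation gives a much smaller number. Either an input is misreported or the calculation used a different scenario. In both cases the reader cannot tell which effect and which variability the design protects against.

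The second part concerns the promised minimum. Reweighting site means to shares other than the enrolled shares increases the variance of the treated mean. Section V.A.1 sizes an unweighted comparison and mentions no such allowance. How much reserve 389 holds against this depends on the inputs behind it, and those are unclear. At stake is the power claim for the trial's only confirmatory test.

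**Working it through.** **Inputs.** From section V.A.1: control mean 28.2, control SD 42.5, reduction 25%, ratio 1.65, power 90%, one-sided alpha 0.025. From the Analysis Summary: 19,446 controls, fixed.

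- Treated mean: 0.75 × 28.2 = 21.15. Difference: 7.05 minutes.
- Treated SD: 1.65 × 21.15 = 34.90.
- z-values: 1.960 + 1.282 = 3.2415.

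**The plan's figures.** The attrition step reproduces: 389/0.86 = 452.3, and 452 + 33 = 485. The 389 does not.

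**Required n with a fixed control sample** (normal approximation):

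n = SD_T² / [(difference/3.2415)² − SD_C²/19,446]

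- (7.05/3.2415)² = 4.730 and 42.5²/19,446 = 0.093, so the denominator is 4.637.
- n = 34.90²/4.637 = 1217.8/4.637 = 262.6, so 263. A Welch t search gives 265.
- If the control SD is also raised to 1.65 × 28.2 = 46.53, n is 263.7, or 266 by Welch t.
- At the observed ratio of 1.50 (treated SD 31.7), n is 217, or 219 by Welch t.

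**Power of 389 under the stated inputs.** SE = √(1217.8/389 + 0.093) = √3.224 = 1.795. Then 7.05/1.795 − 1.960 = 1.967, which gives 97.5% (Welch t: 97.5%, or 97.4% with control SD 46.53).

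**Inputs that do give about 389**, none of them stated in the SAP:

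| Scenario | n (normal approximation) |
|---|---|
| 25% reduction, treated SD left at 42.5 (ratio 2.01) | 389.5 |
| 20% reduction, ratio 1.50 | 390.2 |
| 21.6% reduction (more exactly 21.56%), ratio 1.65 | 389 |
| 25% reduction, ratio 1.65, 97.5% power | 387.6 (389.9 with control SD 46.53) |

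**Effect of site weighting.** Let p_k be the MPOG share and n_k the number of treated subjects at site k. A valid variance of the weighted mean is Σ p_k² s_k²/n_k. With a common within-site SD this equals (SD_T²/n) × D, where D = n Σ p_k²/n_k. D is at least 1 and equals 1 only if enrolment follows the MPOG shares. At n = 389 and ratio 1.65, power is Φ(7.05/√(3.131 D + 0.093) − 1.960):

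| D (assumed) | Power |
|---|---|
| 1 | 97.5% |
| 1.25 | 94% |
| 1.47 | 90% |
| 2 | 80% |

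The limit follows directly: 389/265 = 1.47 by Welch t (389/262.6 = 1.48 by normal approximation).

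**Illustrative site mixes.** These are assumptions, since the SAP gives no shares:

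- Thirteen sites, even enrolment, MPOG shares evenly spaced in the ratio 1 to 14: D is about 1.29, power about 93%.
- Ten sites, even enrolment, MPOG shares proportional to 5, 4, 3, 2, 2, 1, 1, 1, 1, 1: D = 10 × 63/21² = 1.43, power about 91%.
- Ten sites, equal MPOG shares, enrolment proportional to 10, 6, 4, 3, 2, 1, 1, 1, 1, 1: D = 0.01 × 30 × 6.35 = 1.905, power about 82%.

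Plausible mixes therefore fall on both sides of the limit.

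**The case against.** Four points can be made for the plan.

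1. **The mismatch is safe.** Under the stated inputs 389 exceeds the need, so a 90% minimum is true of an unweighted test. This stands. A reader might infer from a sample size that cannot be reproduced that the trial is underpowered, and the document does not support that.

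2. **Other scenarios may lie behind 389.** The reduction is given as approximate, and several SD-ratio computations are mentioned. This also stands, and it limits what can be concluded. A reader might infer that 389 came from leaving the treated SD at 42.5, which would leave no reserve for weighting. That is one match among at least four, and it contradicts the constant-ratio assumption in the same section. It does not rescue the text, however. Ratio 1.65 is the only conservative ratio named, and even a 23% reduction at that ratio needs only 328.

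3. **The weighting loss is hypothetical.** No site shares are given, so no particular D can be charged to the plan. At ratio 1.50 the tolerance is wider (389/217 = 1.79). If site means differ, within-site SDs would be below the overall SD, which offsets part of the loss. All of this stands, so the result is a threshold and not a demonstrated shortfall.

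4. **The variance used here is not the one written in section IX.D.** That section sets s² = Σ(p_k s_k)² and divides by the total n. For ten equal sites this is one tenth of the valid variance. Taken literally, the test would reject more often, not less, with a false-positive rate of about 24% in place of 2.5% (SD 34.9, n = 389). That is a separate fault. The power figures here apply to a correctly computed stratified variance, which section IX.D evidently intends when it calls for a properly computed SD.

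**Conclusion.** The point holds as an error of derivation and an unsupported power statement.

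- **Derivation.** The stated assumptions need 263 to 266 completed subjects. The plan's 389 is about 47% above that (389/265 = 1.47) and gives about 97.5% power before weighting. Rounding, or the choice between t and normal methods, moves the answer by two or three subjects and cannot explain the gap. The inputs really used for 389 cannot be recovered from the SAP.
- **Weighting.** The 90% minimum is not established for the site-standardised test. At ratio 1.65 and a 25% reduction it holds while D is at most about 1.47 and fails above that. This rests on a valid stratified variance, a common within-site SD equal to 34.9, and 389 completed subjects. D itself is an assumption.

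It would go too far to say that power is below 90%. That would need either actual site shares giving a D above the limit or evidence that 389 rests on a larger SD or a smaller effect. The document supplies neither.

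**What to change.** Keep the sample size. In section V.A.1:

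1. State the reduction, treated SD, control SD and power entered in the PASS run that produced 389, taken from the saved output and not reconstructed.
2. State that with a 25% reduction and ratio 1.65, 389 completed subjects give about 97% power for an unweighted comparison.
3. Replace the 90% minimum with power for the site-standardised test over a plausible range of D = n Σ p_k²/n_k, computed from the MPOG site shares and the expected enrolment by site. For the 25%/1.65 case, add that power is at least 90% while D is no more than about 1.47.

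These power figures presume the variance Σ p_k² s_k²/n_k, so section IX.D should be brought into line with it.

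The cost is SAP wording, retrieval of one software output and a short calculation from shares the sponsor needs anyway for the primary analysis. Enrolment does not change.

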## **B. Primary Safety Variable**

The primary safety endpoint is the percentage of serious adverse events to include perioperative events, postoperative complications, and device-related serious adverse events.

### C. Secondary Effectiveness Endpoints

The secondary effectiveness endpoint is the determination total area under the curve of the time and MAP for all time periods for which MAP < 65 mmHG in each subject.

### D. Secondary Safety Endpoints

The secondary safety endpoint is a composite of the following events within 30 days of the procedure: postoperative non-fatal cardiac arrest, in-hospital death, stroke, acute kidney injury (AKI), and myocardial injury in non-cardiac surgery.

### E. Additional Endpoints

#### 2. Reduction of IOH duration at MAP ≤ 60 mmHg.

The duration of IOH considering a lower cut point will be estimated for the study subjects.

#### 3. Area under threshold MAP < 65 mmHg

A measure highly correlated with duration of IOH is the area under the threshold of 65 mmHg. The area is computed by using the trapezoidal rule to estimate the area of pressure and time. The Total AUC is obtained using the formula below.

$$Total\ AUC = \sum_1^k \sum_1^l ((t_{ij} - t_{(i-1)j}) * (65 - (\frac{p_{ij} + p_{(i-1)j}}{2})))$$

where  $t_{ij}$  is the measurement time of the  $i$ th IOH increment of the  $j$ th IOH episode for the patient and  $p_{ij}$  is the mean pressure in mmHG for the  $i$ th IOH increment of the  $j$ th IOH episode. The episode for each patient begins,  $t_{0j}$ , with the first of two successive pressure measurements below MAP 65 mmHG and continues until the MAP raises to 65 mmHG or above. The trapezoidal rule sums the averages the decreases in pressure from 65 mmHG between two measurement times and multiplies that by the difference of the time increment between. Then the areas per episode are summed across the total number of episodes.

#### 4. Acute kidney injury (AKIN criteria).

The percentage of study subjects with acute kidney injury under the AKIN criteria will be estimated.

#### 5. Quality of recovery (QoR-15) on postoperative day 3.

The scores of QoR-15 will be computed and reported.

#### 6. Postoperative morbidity survey (POMS) on postoperative day 3.

The postoperative morbidity will be assessed with the POMS on the third day after surgery.

#### 7. Amount of red blood cells infused (ml packed red blood cells).

The amount of transfused blood product will be estimated and reported for study subjects.

